## 1.2 RATIONALE FOR STUDY

Circadian ('around 24 hour') rhythms orchestrate many biological functions and are driven by molecular clocks that exist in every cell - including cells of the brain. These biological clocks are essential for optimal brain health and the regulation of  $T_{Bo}$ . Emerging evidence suggests that brain cell clocks are disrupted in neurodegenerative diseases such as Alzheimer's disease. The risk of these diseases is highest in elderly individuals, who are notoriously poor at regulating their own temperature. In healthy brain cells, molecular clocks maintain circadian rhythms at constant speed, despite temperature fluctuation. Cold-inducible chaperone (CIC) proteins interact with cellular clocks and are highly sensitive to temperature change. We propose that CICs are critical to clock fidelity under  $T_{Br}$  fluctuation, and that failure of this mechanism advances neurodegeneration. First, we must determine how human  $T_{Br}$  varies with time; this represents a fundamental knowledge gap.

$T_{Br}$  fluctuation is reported in rodents, but circadian effects may be confounded by the sleep-wake cycle.  $T_{Br}$  also depends on cerebral haemodynamics, and given species-specific variation in cerebral circulation, extrapolating animal data to humans is problematic. The current gold standard technique for human  $T_{Br}$  measurement requires an intracranial probe, retrieving data from a focal point in the brain parenchyma. This is reserved for patients undergoing neurosurgery, or those with traumatic brain injury. With MRS, high-resolution  $T_{Br}$  data can now be obtained non-invasively in healthy subjects. Pre-existing round-the-clock  $T_{Br}$  data from brain-injured patients has informed the design of an MRS study in human volunteers, to measure healthy  $T_{Br}$  at different times of the day. Derived maximum and minimum  $T_{Br}$  will be used to explore how CICs are involved in the resilience of clocks to physiological temperature shifts using human stem cell-derived brain cells in the lab, potentially leading to novel therapeutic targets for chronic brain disorders.

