### *Hypotheses:*

- A diurnal shift in mean human  $T_{Br}$  can be measured in healthy volunteers.
- Mean human  $T_{Br}$  exceeds oral temperature, irrespective of time.
- Mean brain and oral temperatures are higher in luteal-phase women than in men.

*Method:* alongside brain injury effects, several confounders limit extrapolation of

patient data to the general population. Using MRS, we will map diurnal changes in  $T_{Br}$  in healthy volunteers to determine normal human maximum and minimum  $T_{Br}$  at unparalleled spatial resolution. Participants will be recruited locally and screened for suitability via electronic questionnaire. If eligible and willing to participate, they will be provided with the Participant Information Sheet and Consent to Participate Form. One visit 7 days prior to scanning will be used as the consenting procedure, and to issue actigraphy wristbands, and also urine test kits (where needed).. 40 subjects (20 men, 20 women) will each be scanned at 3 specific times (morning, afternoon, and late evening) within 24h, using a 3 Tesla MRI scanner. The scanning protocol will include whole brain, T1- and T2-weighted structural acquisition followed by MRS in a superficial and deeper brain location. All scans will be conducted within four months (minimizing seasonal variation) in a temperature-controlled room. Meal times and caffeine consumption will be fixed on the day of scanning and participants will be requested to avoid alcohol and excessive physical activity. Oral temperature will be measured prior to each scan, and hormonal influences controlled through urine testing (naturally cycling women only). Protocols for data extraction and temperature estimation by MRS are already validated and published. Anonymised MRS data will be processed blind (to time of day), and then analysed using a linear mixed model that accounts for time of day, subject-specific chronotype (based on activity data), and repeated measures for each participant.

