#### 2.1.2 Secondary Objectives

- Quantify the difference in variability of brain and oral temperatures across a 24-hour period in healthy human volunteers
- Quantify the difference between healthy male and luteal-phase female  $T_{Br}$  at each time of day
- Quantify the difference between temperatures at the brain surface and the brain core at each time of day in healthy human volunteers

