#### 2.2.2 Secondary Endpoints

- The difference in variation of brain and oral temperatures across a 24-hour period

- The difference in brain and oral temperatures between men and luteal-phase women at each time point
- The difference between deep and superficial  $T_{Br}$  at each time point

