*Null hypothesis (2):* The variability in temperature within a single 24-hour period will not differ significantly between brain and oral regions of healthy human volunteers.

*Alternative hypothesis (2):* Human  $T_{Br}$  variation will exceed oral temperature variation within a single 24-hour period in healthy human volunteers.

There is conflicting data comparing brain and core body temperatures in humans and other animals, but generally,  $T_{Br}$  is considered to exceed core  $T_{Bo}$ , and we have recently observed a greater daily variability in  $T_{Br}$  relative to  $T_{Bo}$  in patients with traumatic brain injury (see References).

*Null hypothesis (3):* There is no statistically significant difference between brain temperatures measured in healthy men and women

*Alternative hypothesis (3):*  $T_{Br}$  will be higher in luteal-phase women and in women taking monophasic contraceptive medication compared to men, after accounting for chronotype differences.

It is established that an increase in progesterone during the post-ovulatory (luteal) phase of the menstrual cycle increases  $T_{Bo}$ , and there is published evidence that women in the luteal phase of their cycle have higher body temperatures throughout the circadian cycle relative to men. There is also evidence to suggest that the synthetic steroids (progesterone and oestrogen) provided in the monophasic contraceptive pill are associated with a persistently increased  $T_{Bo}$  throughout the cycle compared to the  $T_{Bo}$  observed during the natural follicular phase in women not taking oral contraceptives. We predict that this may also be reflected in  $T_{Br}$ , and therefore we would expect luteal-phase women and women taking monophasic contraception to have higher brain temperatures than men, irrespective of the time of the day.

*Null hypothesis (4):* There is no statistically significant difference between mean temperatures at the brain core and the brain surface in healthy human volunteers

*Alternative hypothesis (4):* Mean temperature at the brain core will be consistently higher than that at the brain surface, irrespective of time.

Intuitively, we would expect mean temperature deeper within the brain to exceed that at the brain surface, based on the laws of physics.

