### Study procedure

Each participant will be scheduled to attend for three brain scans (approximate duration 45 minutes) at specific times on a single day (morning, afternoon, and late evening) using a 3 Tesla MRI scanner located in a temperature-controlled room at the Edinburgh Imaging (Royal Infirmary of Edinburgh) Facility. After consent is obtained, all participants will wear an actigraphy wristband for one week prior to scanning to establish their normal rest/activity, skin temperature, and light exposure patterns (and therefore their individual chronotype). On arrival at the imaging facility on their scanning day, each participant will have their height and weight recorded, and their actigraphy wristband will be removed and the data downloaded. Prior to each scan, the participant will be asked to change into hospital clothing and to complete an MRI safety and quality checklist (i.e. no metallic/cochlear implants, no metallic jewellery, no makeup that might create imaging artefacts). The participant's temperature will then be measured with an oral thermometer and if the temperature lies above or below the normal oral temperature range (33.2–38.1 °C for women; 35.7–37.7 °C for men), the participant will be rescheduled for an alternative day and any scans already performed on that participant will be excluded from the analysis. For female participants with natural menstrual cycles, a commercially-available urine testing kit (Clearblue) will be provided to confirm ovulation 7-10 days prior to their scheduled scanning date (several test strips supplied during the consenting interview so that urine can be tested for a luteinizing hormone surge on 3 consecutive days if necessary). Should ovulation not be confirmed, further test strips will be provided and the scans rescheduled for the following month. Kits will not be required for women taking monophasic contraception. No urine samples will be collected or stored from any participant; women using the kits must confirm ovulation by notification to the CI ahead of the planned scanning date, and will have the option of bringing a digital photo of the test result with them on the morning of scanning. The result will be viewed by the CI but no photos will be transferred or stored.

For each scan, the protocol will start with structural imaging of the whole brain using standard structural MRI sequences. The MRS protocol will immediately follow the

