safe method of brain imaging with no known lasting effects on the brain after repeated imaging. Although intravenous contrast methods are sometimes used for MRI diagnostics, contrast is not required for MRS and will not be used in this study. Therefore no invasive procedures will be performed, but the lack of post-contrast imaging means that some HRFs may require follow-up imaging to verify them. The feedback and follow-up pathway is explained in the Participant Information Sheet.

A 3 Tesla (3T) MRI scanner is proposed for this work, because a recent study published by members of the Study Team showed that 3T MRS was more reliable than 1.5T MRS in estimating  $T_{Br}$  in healthy men. In that study, all scans were carried out at the same time of day to control for any effects of diurnal temperature fluctuation. In this study, the diurnal variation in human  $T_{Br}$  is the key parameter of interest and so each volunteer will be scanned at specific times in the morning, afternoon, and late evening on their scheduled scanning date. MRI-based brain imaging remains a fairly time-consuming process requiring high technical skill for acquisition and processing. Repeated brain imaging of each volunteer on a single day places a level of burden on that individual and on staff running the scanner. A three time point design was chosen to maximize the opportunity to meet our primary research objective whilst minimizing the burden on individual volunteers and radiographers. The selected time points are based on preliminary analysis of pre-existing data from human brain injury patients showing when  $T_{Br}$  was recorded at its maximum and minimum level via intracranial probe. Whilst we cannot conclude that  $T_{Br}$  peaks and troughs will occur at these same times in healthy human volunteers, the spacing between the time points should ensure that we do not inadvertently capture two times at which  $T_{Br}$  will be the same within a 24 hour cycle. The selected time points are also sympathetic to volunteer and staff needs, and aim to prevent any disruption to sleep patterns that may affect the results. More frequent sampling would be neither practical, nor cost-effective and would likely present a major barrier to recruitment.

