The inclusion and exclusion criteria have been specifically developed to maximize participant safety, compliance, and wellbeing, whilst controlling for confounding effects that might impact upon  $T_{Br}$  and  $T_{Bo}$ , and/or thermoregulation generally. In particular,  $T_{Br}$  is highly dependent on blood flow to the brain, and on the sleep/wake cycle. We have therefore excluded people with known sleep disorders or with medical conditions that would be expected to affect general circulation, cerebral blood flow, or thermoregulation. Thermoregulation is also known to decline with age and is subject to variation in body mass, and so the age range has been limited to 20-40 years, and the BMI to 18.5-29.9. The proposed age range is consistent with the ages of healthy adult males recruited into the previously published study, and from which  $T_{Br}$  data was successfully acquired through MRS. The inclusion of women is a step forward from the previous study, which excluded women to avoid potential confounding effects of the menstrual cycle on  $T_{Br}$ . For the results of the prospective study to be widely applicable, it is important to include women whilst controlling for these effects. We believe that our approach is scientifically justified, easy to achieve, inexpensive, and logistically feasible within the duration of the study. We accept that for naturally cycling women there will be additional burden (urine testing in a location of their choosing, and a reduced selection of scanning dates) that may impact on their recruitment. However, we believe that this small impact is outweighed by the negative impact on recruitment if these women were to be excluded. Finally, the actigraphy data will allow us to control for differences in chronotype which are known to vary between the sexes, as well as between individuals of the same sex.

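### Three scans between morning and late evening can test for a change in brain temperature, but cannot give the normal maximum and minimum or the 24-hour variability that the protocol promises

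*Protocol*

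**What the plan says.** Promised:

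- The method paragraph under the hypotheses in section 1.2 says diurnal changes in brain temperature will be mapped "in healthy volunteers to determine normal human maximum and minimum" values.
- Earlier in section 1.2, the "Derived maximum and minimum" brain temperature is the input to the stem-cell experiments on temperature and the clock.
- Section 2.1.2 sets as a secondary objective: "Quantify the difference in variability of brain and oral temperatures across a 24-hour period in healthy human volunteers".
- Section 2.2.2 has the matching endpoint: "The difference in variation of brain and oral temperatures across a 24-hour period".
- Alternative hypothesis 2 in section 3 is directional: brain temperature "variation will exceed oral temperature variation within a single 24-hour period in healthy human volunteers".

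Collected:

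- Section 3 (study procedure) schedules three scans per participant "at specific times on a single day (morning, afternoon, and late evening"). No clock times are given. Oral temperature is taken only just before each scan.
- The reasoning for the design, also in section 3, says the chosen times "aim to prevent any disruption to sleep patterns that may affect the results".
- The same reasoning says brain temperature "is highly dependent on blood flow to the brain, and on the sleep/wake cycle".

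**The concern.** The protocol names the sleep/wake cycle as a main driver of brain temperature, then measures only on the waking side of it. The highest and lowest of three waking time points are not the maximum and minimum of the cycle, and the spread between them is not variability over 24 hours.

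This goes beyond style. The derived maximum and minimum are to be carried into laboratory work as the normal human values. If the true minimum falls in the unsampled hours, the laboratory range will be too narrow at its lower end, and nothing in the study's data would reveal it. The secondary objective and endpoint would be reported under a 24-hour label although a large block of the 24 hours has no brain or oral reading. No later analysis can recover hours that were not observed.

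**Working it through.** **1. What the design reasoning supports.** Section 3 bases the scan times on when brain-injured patients reached their maximum and minimum by intracranial probe. It concedes that healthy volunteers may peak and trough at other times. It defends the spacing only on the ground that two scans should not land on the same temperature. Set against the aims:

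| Aim | Needs | Met by three waking scans? |
|---|---|---|
| Primary: does brain temperature change with time of day (2.1.1, 2.2.1)? | Scan times at which temperature differs | Yes, on the protocol's reasoning |
| Normal maximum and minimum (1.2) | Readings at or near peak and trough | Not assured; the times are conceded to be unknown |
| Variability over 24 hours (2.1.2, 2.2.2) | Coverage of the whole cycle | No; the sleep period has no reading |

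**2. Could a fitted curve fill the gap?** A 24-hour cosine has three parameters: mean, amplitude and phase. Three readings per person leave 3 − 3 = 0 residual degrees of freedom. A minimum placed between the late-evening and morning scans would rest wholly on the assumed shape. The wristband records skin temperature before the scanning day, but not brain or oral temperature, and section 6.1 has it removed before the first scan.

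**3. Illustrative size.** The protocol states neither clock times nor the shape of the rhythm, so everything in this step is an assumption:

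- temperature at hour t is c(t) = −cos(2π(t − trough)/24), which runs from −1 to +1
- trough between 02:00 and 06:00
- scans at 9, 16 and 23 h (overnight gap 24 − 14 = 10 h) or at 10, 16 and 22 h (gap 24 − 12 = 12 h)

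Share of true range seen = (highest c − lowest c)/2. Shortfall at the bottom = (lowest c + 1)/2.

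Worked case: scans at 10, 16 and 22 h, trough at 04:00. The values are −cos 90° = 0, −cos 180° = 1 and −cos 270° = 0. Share seen = (1 − 0)/2 = 0.50. Shortfall = (0 + 1)/2 = 0.50.

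Worked case: scans at 9, 16 and 23 h, trough at 02:00. The values are −cos 105° = 0.26, −cos 210° = 0.87 and −cos 315° = −0.71. Share seen = (0.87 + 0.71)/2 = 0.79. Shortfall = (−0.71 + 1)/2 = 0.15.

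| Trough | 9, 16, 23 h: share seen | Lowest scan above true minimum | 10, 16, 22 h: share seen | Lowest scan above true minimum |
|---|---|---|---|---|
| 02:00 | 0.79 | 0.15 | 0.68 | 0.25 |
| 03:00 | 0.73 | 0.25 | 0.61 | 0.37 |
| 04:00 | 0.63 | 0.37 | 0.50 | 0.50 |
| 05:00 | 0.73 | 0.25 | 0.61 | 0.37 |
| 06:00 | 0.79 | 0.15 | 0.68 | 0.25 |

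Over both schedules, 50–79% of the true range is seen, and the lowest scan lies 15–50% of that range above the true minimum.

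**4. In degrees.** Suppose the three time-point means span the 0.5 °C used in the sample size (section 8.1). The true range would then be 0.5/0.79 = 0.63 °C to 0.5/0.50 = 1.0 °C. The lowest mean would lie between 0.15 × 0.63 = 0.09 °C and 0.50 × 1.0 = 0.5 °C above the true minimum.

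**The case against.** **The limits are partly disclosed.** Section 3 accepts that one scanning day cannot cover day-to-day variation. It admits that healthy peaks and troughs may fall elsewhere, and gives practical reasons (sleep, cost, burden, recruitment) against more scans. All of this stands, and no extra scan is asked for. But none of it says that the sleep-period minimum goes unmeasured, and the aims are not narrowed to match.

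**Scope.** The maximum and minimum appear as an aim only in the rationale and method text of section 1.2, not among the objectives or endpoints. Hypothesis 2 speaks of variation within one 24-hour period, which is literally true of three scans on one day. Both points are fair. The overreach lies in section 1.2 and in sections 2.1.2 and 2.2.2; hypothesis 2 needs changing only for consistency.

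**Size.** The percentages depend on assumed clock times, trough and shape. If the peak may fall at any hour, the same calculation gives 63–97% for the first schedule and 50–100% for the second, so the loss could be small if the extremes happen to fall at scan times. The figures illustrate; they do not estimate.

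**Chronotype.** Section 3 plans to normalise to individual chronotype. This realigns readings to each person's clock, but every reading is still taken outside the sleep period.

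**A stronger reading that does not hold.** A reader might infer that the maximum and minimum will be the raw highest and lowest individual readings, and so pushed outwards by scan noise. The protocol does not say so. Sections 1.2 and 8.2 describe a linear mixed model, with the core analysis comparing mean temperature between time points. Such means are hardly affected by scan noise: with a true 0.5 °C linear shift, 36 subjects and assumed scan SDs of 0.2 to 0.74 °C, simulation puts the expected range of the three means at 0.50–0.51 °C.

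**Conclusion.** The point holds as a mismatch between stated scope and data. Three scans from morning to late evening support a test for change between those times. They do not support a normal maximum, a normal minimum or a 24-hour range. With time-point means as the estimates, the error from the unsampled hours runs one way: the range can be understated, not overstated.

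Under the assumptions in the working, the scans see about 50–79% of the true range, and the lowest scan lies 15–50% of that range above the true minimum. The protocol fixes neither the clock times nor the trough, so the true loss could be smaller or larger.

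A reader might also infer that the primary objective is undermined. It is not: it asks only whether brain temperature differs between time points. What is affected is the aim in section 1.2, the use of its result in the laboratory, and one secondary objective with its endpoint.

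**What to change.** - In the method paragraph of section 1.2 and in sections 2.1.2 and 2.2.2, restate the scope as variation between the three scanned times of the waking day. Align hypothesis 2 in section 3 with that wording.
- In section 1.2, define the maximum and minimum as the highest and lowest model-estimated means among the three time points, each with a 95% confidence interval. Name these as the values passed to the laboratory work.
- State once, most naturally beside the day-to-day limitation in section 3, that the minimum during the sleep period is not estimated.

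The cost is a narrower stated scope. No scan, participant or analysis is added, and the mixed model already planned yields the quantities needed.

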## 2 STUDY OBJECTIVES

### 2.1 OBJECTIVES

#### 2.1.1 Primary Objective

To determine whether human  $T_{Br}$  varies according to time of day using a non-invasive brain imaging technique (MRS).

#### 2.1.2 Secondary Objectives

- Quantify the difference in variability of brain and oral temperatures across a 24-hour period in healthy human volunteers
- Quantify the difference between healthy male and luteal-phase female  $T_{Br}$  at each time of day
- Quantify the difference between temperatures at the brain surface and the brain core at each time of day in healthy human volunteers

### 2.2 ENDPOINTS

#### 2.2.1 Primary Endpoint

A statistically significant change in mean human  $T_{Br}$  (across all measured voxels per subject) between time points.

#### 2.2.2 Secondary Endpoints

- The difference in variation of brain and oral temperatures across a 24-hour period

- The difference in brain and oral temperatures between men and luteal-phase women at each time point
- The difference between deep and superficial  $T_{Br}$  at each time point

### 3 STUDY DESIGN

This is a prospective, single-site, cohort study in healthy human volunteers based at the Edinburgh Imaging (Royal Infirmary of Edinburgh) Facility. The study duration is 12 months from the start of recruitment to the completion of data analysis and submission for publication. Data collection will be scheduled over a 4-month period from June to September 2019. The anticipated duration of involvement for each participant is up to 17 days (from the date of obtaining informed consent to participate 7-10 days prior to scanning, to 7 days post scanning in case any adverse events need to be reported to the Study Team). The study length will be longer if scans need to be rescheduled for any participant. All participants will have the option to be notified by email when the results of the study are published (with Open Access).

The first key decision during the study design process was to determine the number of scans to be conducted for each participant. The logistical and financial burden of attending for scans was considered, and even though all participants will be local to the scanning facility, our approach is to minimize the impact of scanning on daily life, work, and family commitments. We decided that each participant should be requested to commit only to one scanning day, and that we would capture data at three time points during that single day. Although this removes the effects of day-to-day variation, it clearly cannot account for it, and this is an accepted risk of our method. The 3 time points were chosen based on available literature relating to  $T_{Br}$  fluctuation in rodents, known  $T_{Bo}$  cycles in healthy humans, and also pre-existing data collected from brain-injured patients as part of routine critical care. A 2-time point approach was considered but carried the risk of sampling twice at the midpoint between the temperature peak and trough. Overall our 3-time point approach, together with normalization of  $T_{Br}$  data to individual participant chronotype, will maximize the opportunity to fulfill our recruitment target and meet primary outcome objectives.

The second key decision was for the inclusion of female participants. Women were excluded from previous studies using MRS to measure  $T_{Br}$  in order to remove the potential confounding effect of the menstrual cycle on body (and possibly brain) temperature. We believe it is important, where possible, to include both sexes in studies of human brain physiology, such that the results of our study are as widely applicable as possible. Whilst it is well established that  $T_{Bo}$  can fluctuate during different stages of the menstrual cycle, and that there is a clear difference in chronotype between sexes at certain life stages, the primary outcome for this study is whether there is an intra-individual shift in  $T_{Br}$  between different times of the day. As such, each individual acts as their own control, and a linear mixed model approach can be used to address the effects of nesting at multiple levels when considering data within and between participants. It is also reasonably straightforward (and inexpensive) to control for chronotype differences (using activity monitors) and the effects of the menstrual cycle (by scanning all naturally cycling female participants at the same respective phase of their cycle i.e. post-ovulatory/luteal phase). Whilst this adds an additional non-invasive measurement (actigraphy) for all participants and an

additional procedure (urine testing) for some female participants, we do not believe this would have more than a negligible impact on subject recruitment. Indeed, it means that unexpected chronotype extremes can be accommodated, and both naturally cycling women and women taking monophasic contraceptive medication can be included in the study. It will impact on logistics, reducing the number of dates on which some female participants are eligible for scanning, but this is a manageable risk within the 4-month duration of data collection. Commercially available ovulation urine testing kits were deemed to be a minimally invasive, inexpensive, and effective means of confirming the luteal phase of the cycle in female participants, in a way that could be readily confirmed and recorded by the CI, without compromising the privacy or health of the participant. Commercially-available actigraphy wristbands are widely validated and increasingly used by researchers as well as the health-conscious general public. The data collected from the wristband will be identifiable only by a unique participant identification number and will be downloaded via USB port to a secure University of Edinburgh computer prior to further processing. The data will be safely destroyed without use by the Study Team if a participant decides not to proceed with scanning.

The final key decision was the choice of method for  $T_{Bo}$  measurement in order to exclude participants with  $T_{Bo}$  beyond the normal range. After discussion of the relative risks and merits of more invasive methods (e.g. rectal temperature) we decided that oral temperature measurement would be widely acceptable to potential participants, would be more reliable than aural temperature measurement, and would be least likely to impact negatively on recruitment.

*Null hypothesis (1):* There is no statistically significant change in human  $T_{Br}$  measured at different times of the day within a single 24-hour period

*Alternative hypothesis (1):* There is a statistically significant diurnal shift in human  $T_{Br}$  within a single 24-hour period

This alternative hypothesis was chosen on the basis of known circadian fluctuation in human  $T_{Bo}$  in healthy humans, recently observed circadian fluctuation in  $T_{Br}$  in brain-injured patients that mimics  $T_{Bo}$  cycling (unpublished), diurnal  $T_{Br}$  fluctuation in rodents, and the ability of 3T MRS to detect small changes in human  $T_{Br}$ .

*Null hypothesis (2):* The variability in temperature within a single 24-hour period will not differ significantly between brain and oral regions of healthy human volunteers.

*Alternative hypothesis (2):* Human  $T_{Br}$  variation will exceed oral temperature variation within a single 24-hour period in healthy human volunteers.

There is conflicting data comparing brain and core body temperatures in humans and other animals, but generally,  $T_{Br}$  is considered to exceed core  $T_{Bo}$ , and we have recently observed a greater daily variability in  $T_{Br}$  relative to  $T_{Bo}$  in patients with traumatic brain injury (see References).

*Null hypothesis (3):* There is no statistically significant difference between brain temperatures measured in healthy men and women

*Alternative hypothesis (3):*  $T_{Br}$  will be higher in luteal-phase women and in women taking monophasic contraceptive medication compared to men, after accounting for chronotype differences.

It is established that an increase in progesterone during the post-ovulatory (luteal) phase of the menstrual cycle increases  $T_{Bo}$ , and there is published evidence that women in the luteal phase of their cycle have higher body temperatures throughout the circadian cycle relative to men. There is also evidence to suggest that the synthetic steroids (progesterone and oestrogen) provided in the monophasic contraceptive pill are associated with a persistently increased  $T_{Bo}$  throughout the cycle compared to the  $T_{Bo}$  observed during the natural follicular phase in women not taking oral contraceptives. We predict that this may also be reflected in  $T_{Br}$ , and therefore we would expect luteal-phase women and women taking monophasic contraception to have higher brain temperatures than men, irrespective of the time of the day.

*Null hypothesis (4):* There is no statistically significant difference between mean temperatures at the brain core and the brain surface in healthy human volunteers

*Alternative hypothesis (4):* Mean temperature at the brain core will be consistently higher than that at the brain surface, irrespective of time.

Intuitively, we would expect mean temperature deeper within the brain to exceed that at the brain surface, based on the laws of physics.

